##### Feasibility of the implementation of the programme and its components

The following indicators will be assessed: a) adoption of the programme, in terms of percentage of health professionals that carry out various different components of the intervention; representativeness, dropout rate, causes and degree of influence of the dropout rate on outcomes; b) reach of the programme, in term of percentage of patients exposed to the programme, dropout rate, causes and degree of influence of the dropout rate on the outcomes; and c) implementation of the components of the programme, in terms of degree to which participating patients had received the various different components of the programme as planned.

#### Data quality and management

The coordination, control of quality of processes related to the study, data management and quality assurance will be the responsibility of the Primary Care Research Unit of Bizkaia. The OGTT will be performed in the corresponding health centres or reference laboratory, and results recorded in patient medical records. Changes in lifestyle habits of participants will be assessed by trained professional interviewers, blind to the assignment of patients to the comparison groups, under the supervision of the research team. Data will remain anonymous and only be used for the purpose of this research. Confidentiality of the subjects participating in the study will be maintained in compliance with the Spanish Organic Law 15/1999 on Personal Data Protection (of the 13^th^ December).

#### Sample size

Considering the most conservative results found among high-risk patients in DM2 prevention projects in other countries [6,7] and the most recent data reported from the DE-PLAN project in Catalonia [24], the expected two-year incidence is 15% in the control group. Assuming that the percentage of people diagnosed with DM2 at 24 months will be 15% and 7.5% in the control and experimental groups respectively, and assuming a proportion of 60% recruited patients in the control group with respect to the total sample, to achieve a power of 80% to detect a 50% reduction in the incidence of DM2 as significant, by a Chi square test for independent samples with a two-sided p < 0.05, we need a recruitment under routine conditions of 355 and 237 patients in the control and intervention centres, respectively. However, if we assume that 15% of participants were to be lost to follow-up and an intra-class correlation of 0.01, given that this is a cluster-randomised clinical trial, the number of patients required would be 653 in the control group and 436 in the intervention group, that is, 1089 in total. A sample of 360 patients, 180 in each comparison group, will provide a statistical power of at least 90% to detect, as significant with p <0.05, differences of 50% in the percentage of patients who follow the minimum recommendations of physical activity and servings of fruit and vegetables.

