#### Participants

##### Primary care centres

In each of the seven health regions in which the Basque Health Service is organized, we selected a convenience sample of two centres, similar in terms of structure and population covered. After explaining the objectives of the project and working plan in a presentation session in each of the candidate centers, those professionals who wanted to collaborate signed a written commitment form individually. The 14 centres have been randomly assigned to the intervention and control groups, stratified on a 1:1 basis for each health region, using computer-generated random numbers provided by the Primary Care Research Unit of Bizkaia, such that in each health region there is one intervention and one control group.

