#### Analysis

Statistical analysis will be carried out using the SAS package (version 9.2; SAS Institute, Cary, NC; 2008). The percentages of diagnosed diabetes at 12 and 24 months after the inclusion in the study will be calculated and the level of association with exposure to the educational intervention, considering the potential confounders, will be assessed. Multiple logistic regression analyses will be performed on the percentage of patients diagnosed of diabetes at 24 months, adjusting for intervention group, socio-demographics (age, sex, etc.), and baseline clinical variables (BMI, BP, lipid profile values, etc.). Odds ratios (ORs) and the corresponding 95% confidence intervals (CIs) will be calculated.

Survival analysis will be used to compare the time until diagnosis of diabetes in the different groups. To assess the univariate association of the time until diagnosis of diabetes with the comparison groups and with other possible predictors, cumulative survival probabilities in the 24 months will be estimated and compared using Kaplan-Meier curves along with the log-rank and Wilcoxon tests (SAS PROC LIFETEST, version 9.2, SAS Institute; 2008). Person-years will be the sum of time under follow-up for all participants before diabetes diagnosis or end of follow-up if free of developing diabetes. Subjects who withdrew from the study will be considered to be at risk for diabetes until their last oral glucose tolerance. However, an effort will be made in order to ascertain a diabetes diagnosis at the end of the study period reviewing patients’ charts. Adjusted hazard ratios (AdHRs) and 95% CIs will be estimated to compare diagnosis of diabetes risks between patients in different groups using Cox proportional hazards models introducing all the variables studied in the bivariate analysis as potential confounders. The proportional hazard assumption will be assessed using graphical techniques and a statistical test based on Schoenfeld partial residuals of the model. In the case of covariates for which the proportional hazard assumption is not satisfied, the Cox model will be extended with time-dependent variables allowing hazard ratios to change over time. Finally, to model the clustered structure of data, a common random effect will be introduced into the Cox’s proportional hazards model. This estimation will be carried out by adaptive Gaussian quadrature method implemented in SAS PROC NLMIXED.

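### The sample size allows for an intra-class correlation of 0.01 but keeps normal quantiles with only 14 centres; at a true two-sided 5% level the power is about 74% (12 df), not 80%

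*Protocol article*

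**What the plan says.** The Sample size section sets the aim as "to achieve a power of 80% to detect a 50% reduction in the incidence of DM2 as significant". The test behind that aim is described in these words: "by a Chi square test for independent samples with a two-sided p < 0.05". Diabetes at 24 months is assumed to be such that it "will be 15% and 7.5% in the control and experimental groups respectively". The allocation of patients is unequal, "assuming a proportion of 60% recruited patients in the control group with respect to the total sample". The first result is "we need a recruitment under routine conditions of 355 and 237 patients in the control and intervention centres, respectively".

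The section then adjusts for the cluster design, assuming "15% of participants were to be lost to follow-up and an intra-class correlation of 0.01", and arrives at 653 control and 436 intervention patients, 1089 in total.

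Under Primary care centres, the article says "The 14 centres have been randomly assigned to the intervention and control groups", 1:1 within each of seven health regions, so each region holds one intervention and one control centre. The Analysis section says that, "to model the clustered structure of data, a common random effect will be introduced into the" Cox model, estimated by adaptive Gaussian quadrature. It names no reference distribution or degrees of freedom for that test.

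**The concern.** A design effect enlarges the variance to reflect correlation within centres. It does not reflect how well that variance is known. The units compared are 7 centres against 7, so an unpaired comparison estimates the between-centre variance on 14 − 2 = 12 degrees of freedom. A comparison that keeps the regional pairs has 7 − 1 = 6. The two-sided 5% critical values are then 2.18 and 2.45, not 1.96. A sample size built on 1.96 overstates the power of any test that holds its level with so few centres.

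The Discussion says that positive results will support rolling the programme out to all Osakidetza centres. The stated 80% also governs how a null result would be read. A reader who takes it at face value would treat a null as stronger evidence against a halving of incidence than the design can give.

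**Working it through.** **Inputs.** From Sample size: p₁ = 0.15 (control), p₂ = 0.075 (intervention), 60:40 allocation, two-sided α = 0.05, power 0.80, loss 15%, ICC 0.01, final numbers 653 and 436. From Primary care centres: 7 centres per arm, one pair per region. Assumed here, because not stated: equal centre sizes within arm and the same ICC in both arms.

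**1. Reproduce the base figure.** Pooled two-proportion formula with normal quantiles, ratio k = 2/3, mean proportion p̄ = 0.6 × 0.15 + 0.4 × 0.075 = 0.12:

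n₁ = [1.96 √(p̄(1 − p̄)(1 + 1/k)) + 0.84 √(p₁(1 − p₁) + p₂(1 − p₂)/k)]² / (p₁ − p₂)²

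= (1.007 + 0.405)² / 0.075² ≈ 354.5, and n₂ = 354.5 × 2/3 ≈ 236.3.

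Rounded up, these are the printed 355 and 237.

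**2. Reproduce the final figure.** 355 × 1.15 × 1.60 = 653.2 and 237 × 1.15 × 1.60 = 436.1. These match 653 and 436. The factor 1.60 is back-solved; the article does not print it. Clustering therefore enters as a multiplier on numbers already computed with 1.96 and 0.84.

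**3. Standardised difference at the planned size.** After 15% loss: 653 × 0.85 ≈ 555 and 436 × 0.85 ≈ 371.

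- Mean analysed centre size: 555/7 = 79.3 and 371/7 = 53.0.
- Design effects, 1 + (m − 1) × 0.01: 1.78 and 1.52.
- Variance, control: 0.15 × 0.85 × 1.783/555 = 0.000410.
- Variance, intervention: 0.075 × 0.925 × 1.52/371 = 0.000284.
- Standard error: √0.000694 = 0.0263.
- Standardised difference: 0.075/0.0263 = 2.85.

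**4. Power for that difference at two-sided 5%.** The t rows use the non-central t distribution. The simulation is beta-binomial with 40,000 runs.

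| Reference | Critical value | Power | Simulation |
|---|---|---|---|
| Normal | 1.96 | 81% | 80.7% |
| t, 12 df (unpaired centres) | 2.18 | 74% | 74.5% |
| t, 6 df (regional pairs, no gain credited) | 2.45 | 66% | 66.6% |

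In the simulation, with no true difference, the two t tests rejected 5.1% and 5.0% of the time, so they hold the level.

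**5. Sensitivity.**

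- Reading the loss as division by 1.15, as in step 2, gives 568 + 379 analysed and 75% on 12 df.
- Unequal centre sizes (assumed coefficient of variation 0.4) lower the 12-df figure to about 71%.
- ICC 0.02 instead of 0.01 lowers it to about 60%.
- The normal-quantile figure is itself 78% with the pooled variance and 81% with the unpooled.

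**The case against.** **Clustering was not ignored.** The words about independent samples might lead a reader to infer that it was. They describe only the first step. The next step inflates by an implied 1.60, and both printed totals reproduce. Nothing is miscalculated within the method chosen; the gap is the missing allowance for few centres.

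**The stated level and power are not strictly incompatible.** If the ICC were known to be exactly 0.01, a chi-square test corrected by the design effect would have a level of about 4.9% and power of about 79%. This stands as a limit on the claim. But the Analysis section plans a random effect, whose variance is estimated from the trial's own centres, so the known-ICC case is not the planned analysis.

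**The article does not commit the clustered model to a normal reference.** A reader might infer this from the use of maximum likelihood by quadrature, and then conclude that the planned test exceeds 5%. No reference distribution is stated, and such detail may sit in an analysis plan not shown. A centre-level comparison judged against 1.96 would reject about 7.4% of the time under the null, but no such comparison is planned. The random-effect Cox model's own error rate was not simulated. That figure is therefore no evidence against the planned analysis.

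**The replacement figure rests on assumptions.** Pairing or covariate adjustment could recover some precision, and the ICC matters at least as much as the degrees of freedom. This stands, and is why the restated power should carry its assumptions. It does not rescue the 80%, because the article claims no such gain in its calculation.

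**Conclusion.** The point holds as a correction to the stated power. With 653 + 436 recruited, 15% loss, ICC 0.01 and equal centre sizes within arm, 14 centres give about 74–75% power at a true two-sided 5% level on 12 df. If the regional pairs are analysed without any credit for pairing, the figure is about 66% on 6 df. The shortfall from 80% is about 6 points in the more favourable case and about 14 in the less favourable one. For scale, 80% on 12 df in the same 14 centres would need about 1,395 recruited patients under these assumptions.

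The verdict depends on the between-centre variance being estimated from the trial. It does not extend to saying that the planned Cox model has an inflated type I error.

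**What to change.** In Sample size, restate the power of 1089 patients in 14 centres as about 74%, for an unpaired centre-level comparison on 12 df with ICC 0.01, 15% loss and equal centre sizes within arm. Give the 66% figure for a paired analysis on 6 df beside it.

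In Analysis, state that the intervention effect in the clustered model is tested against a t distribution with degrees of freedom taken from the number of centres (about 12).

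The cost is wording in two sections, a less favourable stated power and slightly wider intervals. No patients or centres are added.

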#### Analysis

Statistical analysis will be carried out using the SAS package (version 9.2; SAS Institute, Cary, NC; 2008). The percentages of diagnosed diabetes at 12 and 24 months after the inclusion in the study will be calculated and the level of association with exposure to the educational intervention, considering the potential confounders, will be assessed. Multiple logistic regression analyses will be performed on the percentage of patients diagnosed of diabetes at 24 months, adjusting for intervention group, socio-demographics (age, sex, etc.), and baseline clinical variables (BMI, BP, lipid profile values, etc.). Odds ratios (ORs) and the corresponding 95% confidence intervals (CIs) will be calculated.

Survival analysis will be used to compare the time until diagnosis of diabetes in the different groups. To assess the univariate association of the time until diagnosis of diabetes with the comparison groups and with other possible predictors, cumulative survival probabilities in the 24 months will be estimated and compared using Kaplan-Meier curves along with the log-rank and Wilcoxon tests (SAS PROC LIFETEST, version 9.2, SAS Institute; 2008). Person-years will be the sum of time under follow-up for all participants before diabetes diagnosis or end of follow-up if free of developing diabetes. Subjects who withdrew from the study will be considered to be at risk for diabetes until their last oral glucose tolerance. However, an effort will be made in order to ascertain a diabetes diagnosis at the end of the study period reviewing patients’ charts. Adjusted hazard ratios (AdHRs) and 95% CIs will be estimated to compare diagnosis of diabetes risks between patients in different groups using Cox proportional hazards models introducing all the variables studied in the bivariate analysis as potential confounders. The proportional hazard assumption will be assessed using graphical techniques and a statistical test based on Schoenfeld partial residuals of the model. In the case of covariates for which the proportional hazard assumption is not satisfied, the Cox model will be extended with time-dependent variables allowing hazard ratios to change over time. Finally, to model the clustered structure of data, a common random effect will be introduced into the Cox’s proportional hazards model. This estimation will be carried out by adaptive Gaussian quadrature method implemented in SAS PROC NLMIXED.

As for the secondary outcome variables, the differences between the groups will be estimated and 95% confidence intervals calculated. The mean changes of the continuous variables will be compared by Student’s t-tests, while differences in proportions will be compared by chi Square tests. In the case of non-normal distribution of data non-parametric tests will be used. Generalized mixed-effects models will be used to estimate baseline and multivariate adjusted between-group differences, adjusted odds ratios (AORs), and 95% confidence intervals (CIs) at the patient level, taking into account the hierarchical and multi-center structure of data.

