#### Evaluation of results

##### Effectiveness of the intervention among patients

The primary outcome variable will be the relative risk of developing DM2, comparing the accumulated incidence (assessed by the OGTT) in the intervention and control groups after 24 months. The secondary outcome variables will be observed changes at 12 months in a sub-sample of intervention and control patients in: the proportion of patients who meet the recommended aerobic physical activity levels (moderate-intensity physical activity for ≥ 30 minutes 5 days/week or vigorous intensity activity for ≥ 20 minutes 3 days/week), derived from the 7-day Physical Activity Recall questionnaire [27]; and the proportion of patients who consume ≥ 5 servings of fruits and vegetables, assessed by the Mediterranean Diet Adherence Screener (MEDAS) used in the ‘*Prevención con Dieta Mediterránea* (PREDIMED)’ study [28]. Lastly, potential effect-modifying variables will be also measured: age, sex, and level of education, among others.

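### The logistic regression for the 24-month primary outcome has no term for the 14 randomised centres, and the one cluster-adjusted diabetes model (Cox) is not named as primary

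*Protocol article*

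**What the plan says.** All references are to the protocol article.

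- **Unit of randomisation** (Primary care centres): "The 14 centres have been randomly assigned to the intervention and control groups, stratified on a 1:1 basis for each health region". Each of the seven regions has one intervention and one control centre.
- **Primary outcome**: "The primary outcome variable will be the relative risk of developing DM2, comparing the accumulated incidence (assessed by the OGTT"), at 24 months (section Effectiveness of the intervention among patients).
- **Sample size**: it assumes that "the percentage of people diagnosed with DM2 at 24 months will be 15% and 7.5% in the control and experimental groups respectively". The total is then raised for 15% loss and "an intra-class correlation of 0.01, given that this is a cluster-randomised clinical trial".
- **24-month proportion** (Analysis): "Multiple logistic regression analyses will be performed on the percentage of patients diagnosed of diabetes at 24 months, adjusting for intervention group", together with socio-demographic and baseline clinical covariates. Odds ratios and 95% confidence intervals are reported. No centre effect, random intercept or robust variance is mentioned.
- **Time to diagnosis** (Analysis): "Kaplan-Meier curves along with the log-rank and Wilcoxon tests" as a univariate step, then adjusted Cox models. Last, "to model the clustered structure of data, a common random effect will be introduced into the" Cox model.
- **Secondary outcomes** (Analysis, final paragraph): "differences in proportions will be compared by chi Square tests", followed by generalised mixed-effects models that allow for the multi-centre structure.

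No analysis is named as primary.

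**The concern.** Patients in the same centre share staff, catchment population and local practice, so their outcomes are correlated. The intervention is allocated to whole centres, so that correlation enters the treatment contrast directly. A patient-level logistic regression treats the patients as independent and understates the standard error of the intervention effect.

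The sample size pays for clustering, but the model that matches the primary outcome does not use it. The same section specifies clustering for the Cox model and for the secondary binary outcomes, so the omission is hard to put down to a journal article's brevity. Clustered and unclustered results for the same diabetes endpoint would then stand side by side, with no rule for which one decides.

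The Discussion says that positive results will support extending the programme to all Osakidetza centres. A chance difference between two sets of seven centres could be read as a programme effect.

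**Working it through.** **1. The plan's own figure.** A two-sided 5% chi-square test without continuity correction, 15% against 7.5%, 80% power and a 60:40 split gives 355 control and 237 intervention patients. This matches the plan exactly (592 in total, power 80.1%). These 592 assume independent patients.

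**2. The clustering allowance in the plan.** The step from 592 to 1089 implies a design effect of 1089 × 0.85 / 592 = 1.56. The planners therefore expected the variance to be about 1.5 times the independent-patient variance.

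**3. Patients analysed per centre** (planned numbers less 15% loss, seven centres per arm, equal centre sizes within an arm assumed):
- Control: 653 × 0.85 = 555, and 555 / 7 = 79.3
- Intervention: 436 × 0.85 = 371, and 371 / 7 = 52.9

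**4. Design effects at ICC 0.01**, from 1 + (m − 1) × ICC:
- Control: 1 + 78.3 × 0.01 = 1.783
- Intervention: 1 + 51.9 × 0.01 = 1.519

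**5. Variance ratio for the difference between arms under no effect:**

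(1.783/555 + 1.519/371) / (1/555 + 1/371) = 1.625, so the standard-error ratio is √1.625 = 1.275.

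**6. Type I error of a nominal 5% test that ignores centre:**

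2 × [1 − Φ(1.96 / 1.275)] = 2 × [1 − Φ(1.538)] = 0.124.

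A nominal 95% interval would cover about 100 − 12.4 = 87.6%. A beta-binomial simulation (7 + 7 centres of 79 and 53 patients, 15% incidence, 200,000 replicates) gave 12.6%. With the plan's implied design effect of 1.56, the closed form gives 11.7%.

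**7. Range.** The plan gives only ICC 0.01. The other rows are assumptions.

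| Assumption | Variance ratio | SE ratio | Type I error |
|---|---|---|---|
| ICC 0.005 | 1.312 | 1.146 | 8.7% |
| ICC 0.01 (plan) | 1.625 | 1.275 | 12.4% |
| ICC 0.02 | 2.250 | 1.500 | 19.1% |

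**8. Region pairs.** If half the between-centre variance at ICC 0.01 is common to the two centres of a region, that half cancels from the difference between arms. The design effects become 0.99 + 79.3 × 0.005 = 1.386 and 0.99 + 52.9 × 0.005 = 1.255. The variance ratio is 1.307, the SE ratio 1.143 and the type I error about 8.7%.

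**9. Power of a clustered test** at 1089 recruited, ICC 0.01 and 15% against 7.5%: about 78% with a normal reference, and about 71% with a t reference on 14 − 2 = 12 degrees of freedom.

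**The case against.** The strongest reply is that the plan does deal with clustering. The last and most developed diabetes model is a Cox model with a random effect, fitted by adaptive Gaussian quadrature, and the section never says that the logistic regression is the deciding analysis. This stands in part. A reader might infer that clustering is ignored throughout the plan, and the document does not support that. But the Cox model estimates a hazard ratio for time to diagnosis, not the 24-month cumulative-incidence comparison that defines the primary outcome, and it is not named as primary either.

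Three further replies limit the point:

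- **Log-rank and Wilcoxon tests.** They are introduced as a univariate step before the Cox model, not as the confirmatory test. It is enough to label their p-values descriptive.
- **Secondary outcomes.** The simple t and chi-square tests are followed by mixed models that account for centre. They should not be counted as an uncorrected error.
- **Size.** The 12% applies to an unadjusted comparison of 7 against 7 unpaired centres. The model in the plan adjusts for patient covariates, and the centres were paired within region and chosen to be similar. Both features can reduce the residual between-centre variance, so 12% is not the error rate of the exact model specified.

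The full analysis plan is not shown and could add a centre term. The article as it stands nevertheless assigns clustering to two other analyses and not to this one.

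**Conclusion.** The point holds in this limited form: as written, the 24-month logistic regression of the primary outcome does not account for the randomised centres, and no cluster-adjusted analysis is designated to decide the primary conclusion.

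At the plan's own ICC, the unclustered standard error is too small by a factor of about 1.27 and the type I error is about 12% instead of 5%. This rests on 15% loss, equal centre sizes within each arm, and no adjustment or pairing. A reasonable range is about 9% (ICC 0.005, or half the between-centre variance shared within regions) to 19% (ICC 0.02). Covariate adjustment may bring it lower by an amount that the document does not allow one to calculate.

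**What to change.** 1. Make the 24-month primary analysis a centre-clustered model: logistic regression with a random centre intercept, or generalised estimating equations with a small-sample-corrected sandwich variance.
2. Include health region as the stratification factor and base the degrees of freedom on the 14 centres, not on the number of patients. Fix the rule in advance, because the choice matters: 12 degrees of freedom if the centres are treated as unpaired, 6 if they are analysed as seven pairs.
3. State that this analysis decides the primary conclusion and that the random-effect Cox model is supportive.
4. Label p-values from the unclustered logistic, log-rank and Wilcoxon analyses as descriptive.
5. For the secondary outcomes, let the mixed models already planned carry the inference. Nothing else need change there.

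**Cost.** No new data are needed. Intervals become wider and power falls below that of an unclustered test, because a t reference on few centres is stricter than z. By the calculation above, power is about 71% on 12 degrees of freedom, against the 80% planned. With 6 degrees of freedom the reference is stricter still, although variance shared within regions would offset part of the loss.

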### Study design

This is a phase IV randomized cluster clinical trial conducted in 14 Osakidetza primary care centres, randomly assigned to the intervention or control groups. The same system for identifying high-risk patients will be set up in all the centres, based on the administration of the 8-item Spanish version of the validated European Finnish Diabetes Risk Score (FINDRISC) [25]. Non-diabetic patients aged between 45 and 70 years old who are identified as at high-risk of developing DM2 (FINDRISC score ≥14) will be invited to participate in a follow-up programme lasting 24 months with annual medical check-ups. Additionally, a sub-sample of included patients will complete an independent, telephone interview carried out by blind external interviewers on dietary habits and level of physical activity at baseline and again after 12 months.

Primary care nursing professionals from the seven intervention centres have set up the DE-PLAN programme (for the intervention groups, IGs), adapted to the setting and normal working conditions in the health centres in OSAKIDETZA. Patients found to be at high risk of developing DM2 (FINDRISC score ≥ 14) who then complete the baseline assessments at these intervention centres will be invited to participate in the DE-PLAN programme; while those in the control health centres, will receive usual care for the prevention and treatment of DM2 (Figure 1).

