#### Recruitment process

The 14 centres will implement a system for identification and screening of all eligible patients based on the FINDRISC scale. Eligible individuals with no exclusion criteria who have a score ≥ 14 on the FINDRISC scale, indicating that they are at high risk of developing DM2, will be invited to participate in the study and given the patient information sheet. This explains that they will be followed-up for a period of 24 months with annual medical check-ups consisting of blood lipid profile and glucose tolerance tests. In addition, to those belonging to intervention centres it provides information on the intervention protocol. Patients who agree to participate and sign an informed consent form, will be invited to perform an oral glucose tolerance test (OGTT) with 75 g of glucose in accordance with the WHO guidelines and a determination of lipid profile and HbA1C. Centre’s nurses will measure body weight, height, and waist circumference. Patients who after the test are diagnosed with DM2 will be seen by their family physician and excluded from the study. High-risk patients with glucose levels below 200 mg/ml in the OGTT will be included in the study.

A sub-sample of consecutive included patients once a full implementation of the program in centres is guaranteed (e.g., three months after study initiation), will undergo an independent baseline assessment by blind certified interviewers of their dietary habits and level of physical activity. In order to minimise selection bias, interviewers will make up to six telephone calls at different times of day and on different days in the week in an attempt to contact these individuals, until they are interviewed or are classified as “not contactable”. Non-contactable patients will not be substituted.

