#### Intervention standardisation

##### Common treatment for both groups in the study

Both comparison groups will implement the same procedures for screening and initial assessment (clinical examination, blood lipid analysis, and an OGTT with 75 g of glucose, following the WHO guidelines) as well as annual check-ups at the health centres.

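### The time-to-diagnosis analysis appears to count chart-found diabetes after at-risk time has stopped, with no matching time for chart-negative withdrawals

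*Protocol article*

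**What the plan says.** Three consecutive sentences of the protocol article, Analysis, set the time at risk:

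- The general definition: "Person-years will be the sum of time under follow-up for all participants before diabetes diagnosis or end of follow-up if free of developing diabetes".
- The rule for withdrawals: "Subjects who withdrew from the study will be considered to be at risk for diabetes until their last oral glucose tolerance".
- A sentence that opens with a contrast and adds that "an effort will be made in order to ascertain a diabetes diagnosis at the end of the study period", by reviewing patients' charts.

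The endpoint is time to diagnosis: "Survival analysis will be used to compare the time until diagnosis of diabetes in the different groups". Cumulative probabilities are "compared using Kaplan-Meier curves along with the log-rank and Wilcoxon tests", followed by Cox models, the last with a random effect for clustering. OGTTs come once a year: participants are "followed-up for a period of 24 months with annual medical check-ups consisting of blood lipid profile and glucose tolerance tests" (Recruitment process), and Common treatment for both groups gives both arms the same schedule.

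The primary outcome, under Effectiveness of the intervention among patients, is the relative risk from 24-month cumulative incidence by OGTT.

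**The concern.** The second and third sentences do not fit together. Under the withdrawal rule, a patient who leaves and stays free of diabetes stops contributing at the last OGTT. If the chart search produces an event for a patient who leaves and later develops diabetes, that event falls after the same cut-off. Events beyond the last OGTT then enter the numerator, while the years lived free of diabetes by the other withdrawals stay out of the denominator.

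The extreme case is a patient who leaves before month 12. The last OGTT is the baseline one, so that patient has no time at risk at all and appears only on becoming a case.

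At stake are the incidence rates in both arms and, if withdrawal differs by arm, the rate ratio and the hazard ratio. The Cox model with a random effect is the only diabetes analysis for which the article names an allowance for clustering, so its result is likely to be read closely.

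**Working it through.** **Inputs from the article (Sample size).** 24-month risk of 15% in control and 7.5% in intervention; 15% loss overall, with no split by arm. These risks reproduce the stated sample size before inflation. With a 60:40 split the pooled risk is 0.12, and the control group needs [1.960·√(0.12·0.88·2.5) + 0.842·√(0.1275 + 1.5·0.069375)]² / 0.075² = 354.5, so 355, and 2/3 of 354.5 gives 237. The article gives no figure for the censoring rule itself.

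**Assumptions not in the article.** Constant hazard; OGTTs at exactly 12 and 24 months; half of withdrawals before and half after the 12-month OGTT; the same hazard in withdrawals as in completers; charts find a share s = 0.8 of diabetes arising between the last OGTT and month 24; the withdrawal splits below.

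**Step 1: constants at 15% risk.** h = −ln(0.85)/2 = 0.08126 per year; p1 = 1 − e^(−h) = 0.07805; p2 = 0.15.

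**Step 2: OGTT events only, censored at the last OGTT.** With a share w withdrawn, per patient:

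- events E = (1 − w)·p2 + (w/2)·p1
- years T = (1 − w)·(2 − p1) + w/2

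Because p2 = p1·(2 − p1), E/T = p1 for every w: 7.80 per 100 person-years. The ratio under no effect is 1.00 at any split.

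**Step 3: add chart cases, with no time for chart-negative withdrawals.**

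- extra events: s·(w/2)·[(p2 − p1) + p2] = 0.8·(w/2)·0.22195 = 0.08878·w
- mean time from last OGTT to diagnosis, summed over the two kinds of withdrawal: 0.03549 (left after month 12) + 0.14594 (left before) = 0.18143, where the terms are ∫(t − 1)·h·e^(−ht) from 1 to 2 and ∫t·h·e^(−ht) from 0 to 2
- extra years, for cases only: 0.8·(w/2)·0.18143 = 0.07257·w

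| Withdrawn | Events | Years | Rate per 100 |
|---|---|---|---|
| 10% | 0.13890 + 0.00888 = 0.14778 | 1.77976 + 0.00726 = 1.78702 | 8.27 |
| 15% | 0.13335 + 0.01332 = 0.14667 | 1.70866 + 0.01089 = 1.71955 | 8.53 |
| 20% | 0.12780 + 0.01776 = 0.14556 | 1.63756 + 0.01451 = 1.65208 | 8.81 |
| 30% | 0.11671 + 0.02663 = 0.14334 | 1.49537 + 0.02177 = 1.51714 | 9.45 |

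Ratio under no effect: 8.81/8.27 = 1.065 (10% control, 20% intervention) and 9.45/8.53 = 1.108 (15% and 30%). A simulation with 2,000,000 patients per arm and withdrawal uniform over 24 months gives 1.060 and 1.108. The Cox hazard ratio moves alike, to about 1.06 and 1.12. Equal withdrawal gives 1.00.

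**Step 4: range.** If chart cases are dated at the last OGTT and charts find 50% to 100%, the ratio is 1.045 to 1.087 at 10% versus 20%, and 1.09 to 1.18 at 5% versus 25%. Under the planned effect, where annual detection gives 0.490, it becomes 0.512 to 0.533 at 10% control and 20% intervention, and 0.469 to 0.451 with the split reversed.

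**Step 5: credit every chart-reviewed withdrawal to month 24.** Events are as in step 3. The years added to step 2 are (w/2)·[(1 − p1) − s·(p2 − p1) + s·0.03549 + 2·(1 − s·p2) + s·0.14594] = (w/2)·2.7695. Rates at 10%, 20%, 15% and 30% are 7.70, 7.60, 7.65 and 7.50, so the ratios are 0.987 and 0.980. If charts are complete, both are about 1.00.

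**Step 6: annual dates taken as exact times.** With no withdrawal, the rates 8.13 and 3.90 (ratio 0.480) become 7.80 and 3.82 (ratio 0.490). Under no effect the ratio stays 1.00, and step 2 shows that it does not depend on withdrawal.

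**The case against.** The article never says that a chart diagnosis is an event, what date it gets, or that chart-negative withdrawals keep the earlier censoring date. The contrast that opens the chart sentence could mean that known end-of-study status replaces the last-OGTT default for everyone. The general person-years definition treats cases and non-cases alike, and such coding is often left to an analysis plan. This stands in part: the faulty rule is inferred, not stated. But the article chose to state a censoring rule, and its two halves are not reconciled. No sentence gives chart-negative withdrawals more time.

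Unequal withdrawal is also an assumption. The article gives 15% overall, and at equal withdrawal the ratio is unbiased. A reader might infer that the intervention arm must lose more because only it has group sessions. Leaving the sessions is not leaving the study, however: follow-up is the annual check-up, common to both arms. The Discussion foresees losses but no imbalance, and the feasibility section plans to examine the influence of dropout on outcomes. All of this stands, so the direction of any bias cannot be predicted.

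Finally, the last-OGTT rule with OGTT events only also leaves patients who withdraw before month 12 without time at risk: 7.5% of an arm at 15% withdrawal, if half leave before then. That is a real limit of the fix. It loses information, but it does not bias the ratio if withdrawal is unrelated to diabetes risk.

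**Conclusion.** The point holds for the time-to-diagnosis analysis. As written, the plan appears to count chart-found cases after the clock has stopped, without matching time for other withdrawals. At 15% withdrawal and 80% chart sensitivity, this lifts the rate at the control risk from about 7.8 to 8.5 per 100 person-years. With no true effect, the ratio is about 1.06 at 10% versus 20% withdrawal, 1.11 at 15% versus 30%, and 1.00 at equal withdrawal. The withdrawal splits and the chart sensitivity are assumptions, and so is an equal hazard in withdrawals and completers. The shift is modest against a planned halving.

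Two stronger readings are not supported. One is that the primary result is biased by this rule: the primary comparison is of 24-month cumulative incidence and uses no person-time. The other is that treating annual detection dates as exact times causes bias when withdrawal differs by arm. With OGTT events only, the ratio is the same at every split, the schedule is common to both arms, and the endpoint is time to diagnosis, not onset. The annual dating moves the planned ratio only from 0.480 to 0.490.

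**What to change.** State one rule that applies to cases and non-cases.

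- **Main time-based analysis:** OGTT-detected events only, censored at the last OGTT. A discrete-time model with intervals ending at 12 and 24 months, a complementary log-log link and a centre random effect is preferable, because event times are tied at the annual visits. It still yields a hazard ratio.
- **Sensitivity analysis:** add chart diagnoses, and credit every chart-reviewed withdrawal, case or not, with time at risk: to diagnosis for cases and to the chart-review date for the others. Report the share of withdrawals whose charts were reviewed, by arm. If charts miss cases, this analysis leans slightly the other way (0.98 to 0.99 in the two scenarios at 80% sensitivity).

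The cost is a change of wording and one more date to record: the chart-review date for all reviewed withdrawals, not only for those found to have diabetes. The downsides are that chart-found events leave the main time-based analysis, and that patients who withdraw before the 12-month OGTT contribute only to the sensitivity analysis.
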